### Trial design {8}

A single-centre, prospective, single blinded, parallel group, 1:1 individually randomised controlled trial. Study duration is 48 months (maximum). Participants and practitioners will not be blinded, but the assessors will be completely blinded, as we describe in the section on ulcer measurements. Each participant will be followed up for up to 6 months from the point of randomisation. Consent (see ethics) and baseline data collection will precede randomisation. A summary of the study pathway is shown in Fig. 1.

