#### Outcomes {12}

The main end-points will be:
‘Rate of healing’ based on two observations per week of ulcer size censored at 42 days (cm^2^ per unit time). We will estimate the effect of the intervention on the change in the ulcer size per unit time, i.e. the rate of healing (see Statistical Analysis).Time to complete re-epithelialization (right-censored at 42 days).

Both end-points will be analysed with and without adjustment for baseline characteristics (trial ulcer area and participants’ age), but we prefer unadjusted outcomes in randomised studies and therefore declare them as ‘primary’.

Secondary end-points:
Rate of healing based on two observations per week up to 70 days (cm^2^ per unit time) (calculated as described below).Time to complete re-epithelisation (observed up to 70 days).Generic quality of life (QoL) measured at first dressing change, fortnightly during in-patient stay and at 6-month follow-up, using the EQ-5D 3L. This scale has previously been used and validated in a Nepali population [17]. As far as we are aware, there is no valuation tariff in the Nepalese population, although this may change by the time that the analysis starts. Therefore, we propose not to prespecify the tariff but instead select the tariff at a later date. We note that tariffs are currently available for nearby countries including Sri Lanka [18] and China [19, 20].Longer-term outcomes measured at 6-month follow-up from randomisation will be proportion with:
i.Recurrence of treated ulcer;ii.Appearance of new ulcer;iii.Anatomical changes in the limb;Days hospitalised prior to discharge and total (to include any readmission due to leprosy/ulcers) by 6 months.Health economic information:
i.Number of visits to any healthcare facility from discharge to the end of follow-up at 6 months.ii.Data on the time taken to change dressings at the twice weekly changes.

Rate of healing will be assessed from blindly assessed photographs (Fig. 2). However, as complete healing may trigger discharge, we will monitor for cases discharged before the blinded assessor in Birmingham has noted complete re-epithelization.

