### Assignment of interventions: blinding

#### Who will be blinded {17a}

The Nepal research team, the database managers in Birmingham, the clinical staff carrying out dressing changes in the room designated for this purpose and participants themselves will be aware of participants’ randomly assigned group. Ward staff will not be informed. Researchers in Birmingham involved in the data analyses will be blinded to treatment allocation (Fig. 2).

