### Data collection and management

#### Plans for assessment and collection of outcomes {18a}

Demographic data (age and sex), clinical data (number and size of ulcers), concurrent diseases will be collected for all consenting participants before randomisation (Fig. 1). Data on quality of life (QoL) will be collected fortnightly from first dressing change until discharge. Ulcers will be assessed twice weekly (see below) during the participant’s hospital stay, to a maximum of 70 days, and then again at a 6-month follow-up visit. Steps taken will be collected daily until 42 days (the point where cross-over may occur) or discharge, whichever comes first. Follow-up data collection at 6 months will require an outpatient appointment or a home visit (Fig. 3). Data, including photographs of ulcers, will be collected on electronic tablets using the Research Electronic Data Capture (REDCap) system by local researchers.

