### Ulcer measurements

Standardised photographs [23] will be taken twice weekly during inpatient stay dressing changes for participants in both intervention and control groups. Photographs will be obtained in Nepal using two different methods (Fig. 4). The photographs will be transferred to the University of Birmingham and the ulcer dimensions measured in three ways. Two observers will be trained to take these measurements. Both observers will be blinded to the participant’s allocated treatment. All photographs from a given participant will be assigned to the observers at random, separately for the two methods of photography. So that the measurements are not all relegated to the end of the study, they will be made in batches of ten participants reaching completion of their baseline treatments (at complete re-epithelization or 70 days from randomisation). A proportion (20%) of all ulcer photographs will be measured by both observers to test inter-rater reliability. These photographs will be selected at random.

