**Fig. 4 Fig4:**
[figure not shown]
Ulcer capture and measurement process

The date at which complete re-epithelization took place will be determined by the local clinician. Photographs will be taken at the point of complete re-epithelialization and during the follow-up visit.

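### The 6-month recurrence, new-ulcer and limb-change outcomes are collected by staff who know the allocation, and no blinded reading of the follow-up photograph is made the basis of any of them

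*Protocol article*

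**What the plan says.** All references are to the protocol article.

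- **Outcomes {12}** introduces the three outcomes among the secondary end-points: "Longer-term outcomes measured at 6-month follow-up from randomisation will be proportion with" recurrence of the treated ulcer, a new ulcer, and anatomical changes in the limb. In that section, blinded photographs are attached to rate of healing only.
- **Plans for assessment and collection of outcomes {18a}** says how the visit takes place, "Follow-up data collection at 6 months will require an outpatient appointment or a home visit", and who records the data: "Data, including photographs of ulcers, will be collected on electronic tablets using the Research Electronic Data Capture (REDCap) system by local researchers".
- **Who will be blinded {17a}** lists those who know the arm. The list begins "The Nepal research team, the database managers in Birmingham, the clinical staff carrying out dressing changes" and ends "participants themselves will be aware of participants’ randomly assigned group". Ward staff are not told, but they are not described as conducting the 6-month visit.
- **Ulcer measurements** describes two blinded Birmingham observers who measure ulcer dimensions. On timing, "they will be made in batches of ten participants reaching completion of their baseline treatments", which the text defines as complete re-epithelialisation or 70 days from randomisation.
- **Ulcer measurements, text after Fig. 4**, adds: "Photographs will be taken at the point of complete re-epithelialization and during the follow-up visit". It names no reader, reading time or use for the follow-up image.

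**The concern.** Whether a healed site has broken down again, or whether a fissure or small lesion counts as a new ulcer, is a judgement. As written, it falls to people who know the arm, in a hospital that already uses L-PRF (Background and rationale {6a}), with a participant who also knows the arm. The Discussion recognises this risk for the local decision on complete re-epithelialisation and gives it as the reason for central blinded measurement. The same reasoning applies at 6 months, but the protection is not carried over, although a photograph is taken at that visit. At stake is detection bias in the comparison of recurrence, new ulcers and limb change between arms.

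**Working it through.** **1. Who decides, and blind or not**

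| Element | Rate of healing | 6-month outcomes |
|---|---|---|
| Data captured by | Local team, photographs | Local researchers, clinic or home visit |
| Judged by | Two blinded observers in Birmingham | No blinded assessor named |
| What the blinded reading yields | Ulcer area (cm²) | No coding of recurrence, new ulcer or limb change described |
| Timing of blinded reading | Batches at healing or day 70 | None stated |

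Birmingham analysts are blinded under {17a}, but that does not remove a judgement already made at data collection.

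**2. Does the written batch trigger reach the 6-month image?**

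Inputs: 130 participants (Sample size {14}: 65 per group); recruitment of 12–18 months (Trial status); batches of ten; latest trigger at day 70. A month is taken as 30.4 days and 6 months as about day 182.

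Time to accrue ten participants = 10 / (130 / months) × 30.4.

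- 12 months: 10 / 10.83 × 30.4 ≈ 28 days, so the batch is complete by about day 70 + 28 = 98 after its first member's randomisation.
- 18 months: 10 / 7.22 × 30.4 ≈ 42 days, giving about day 70 + 42 = 112.

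Both fall before day 182. The stated trigger alone does not bring in the follow-up photograph.

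**3. Possible size**

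The documents give neither a recurrence rate nor a misclassification rate, so both are assumed: true recurrence p = 20% or 30% in both arms, and a share m = 10%, 20% or 30% of L-PRF recurrences not called. The spurious difference is p × m. With p' = p(1 − m), SE = √[p(1 − p)/65 + p'(1 − p')/65].

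| p | m | Spurious difference (points) | SE (points) | Ratio |
|---|---|---|---|---|
| 20% | 10% | 2 | 6.9 | 0.3 |
| 20% | 20% | 4 | 6.7 | 0.6 |
| 20% | 30% | 6 | 6.6 | 0.9 |
| 30% | 10% | 3 | 7.9 | 0.4 |
| 30% | 20% | 6 | 7.8 | 0.8 |
| 30% | 30% | 9 | 7.6 | 1.2 |

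Only healed ulcers can recur, so 65 per arm is generous. With the planning values for healing by day 42 (70% and 90%), the denominators are 0.70 × 65 = 45.5 and 0.90 × 65 = 58.5. At p = m = 30%, SE = √(0.21/45.5 + 0.1659/58.5) = 8.6 points, and the ratio falls from 1.2 to 9/8.6 ≈ 1.0.

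**The case against.** The strongest reply is that the blinded process may already cover the follow-up image. Ulcer measurements assigns all of a participant's photographs to the observers, and the Digital tablet section says all observations are made blind. Batching is meant to avoid leaving all measurement to the end of the study; nothing bars a later reading. The process and schedule figures (Figs. 2, 3 and 4) are not available here. This stands: a reader might infer that the 6-month photographs are excluded from blinded reading, and the text does not support that. Even on the generous reading, though, the observers return an area, and no sentence turns it into the recurrence or new-ulcer outcome.

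A reader might also infer a contradiction with Trial design {8}, where "the assessors will be completely blinded". That sentence goes on to refer to the ulcer-measurement section, so it does not promise blinded assessment of every secondary outcome, and {17a} openly lists the Nepal team as unblinded. There is no contradiction.

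A third inference would be that biased recurrence data enter the cost-effectiveness result. The Economic evaluation section links effectiveness to the primary end-point and quality of life and does not mention recurrence, so this is unsupported.

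Two limits also stand. The photographs described are of the ulcer, with no whole-foot views, so they may not show new ulcers elsewhere or limb change. And a condensed article may leave operational definitions to the full protocol. Who judges an outcome, and whether blind, is however a design matter that this article sets out to settle, and for these outcomes it puts collection with unblinded staff.

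**Conclusion.** The point holds for three secondary outcomes. Under {17a} and {18a} they are collected by staff who know the allocation, and no blinded reading is made the basis of any of them. The resulting detection bias is avoidable for recurrence of the treated ulcer, because a photograph is taken at follow-up and blinded observers are already in place. It is avoidable only in part for new ulcers, and on the described imaging not for anatomical change.

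Under the assumed rates the artefact runs from 2 to 9 percentage points, or roughly 0.3 to 1.2 standard errors: modest at the lower end and not negligible at the upper. These figures illustrate the scale and do not estimate the bias; they also assume that misjudgement runs only in favour of L-PRF. The photograph-based primary rate of healing is not affected.

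**What to change.** In Ulcer measurements, including the text after Fig. 4, state that:

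1. the follow-up photographs go to the two existing blinded Birmingham observers in a later batch, after the 6-month visits;
2. the observers code recurrence of the treated ulcer, and a new ulcer where one has been photographed, against the last inpatient image;
3. this masked coding is the analysed recurrence outcome, with the local verdict as a sensitivity analysis;
4. new ulcers outside the frame and anatomical limb changes remain unblinded local assessments, and are to be reported as such.

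If the full protocol already provides for this, adding those statements to the article is enough.

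Cost: at most 130 further readings by existing observers, with no new visit or staff. The drawback is that a photograph may miss what direct examination shows, which is a reason to keep and report the local verdict alongside.

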### ARANZ® SilhouetteStar photography

For the first two measurement methods, a photograph will be taken using the ARANZ® SilhouetteStar device (camera) and the image synchronised to the participant’s trial number and saved to the secure ARANZ® SilhouetteCentral SQL server. This will be assessed by a designated observer at the University of Birmingham. The validated ARANZ 3D wound measurement software tool will then be used to measure the ulcer in two ways. The first measurement will be made using a manual tracing method whereby the ulcer boundary will be ‘hand’ drawn in the ARANZ® software. The software will then calculate the ulcer dimensions based on this outline. The second measurement will utilise an automatic tracing feature in the software. In this instance, the observer will delineate a region of interest (extending beyond the boundary of the ulcer) and the software will automatically locate the boundary and calculate the wound dimensions.

### Digital tablet

The final measurement will use a photograph taken using the in-built camera in the tablet devices (Samsung Galaxy Tab S6). The photograph will be taken perpendicular to the ulcer. For calibration purposes, a 3-cm size clean paper ruler with date and participant’s trial identification number will be placed in the photograph frame above or below the ulcer but at the level of the skin. The photograph will uploaded to the server at the University of Birmingham and evaluated digitally by a designated observer in Birmingham using the PictZar™ Digital Planimetry Software [24] with an electronic PUSH Tool (National Pressure Injury Advisory Panel (NPIAP) at https://npiap.com/page/PUSHTool). The observer will delineate an area of interest by manually ‘painting’ the ulcer area with colour using a computer mouse. The software will then calculate the ulcer dimensions based on this profile.

All observations will be made blind to treatment allocation. The ‘closed loop’ ulcer assessment process is shown in Fig. 2. The changes in surface area can then be determined between each observation using three methods of assessment (Fig. 4).

#### Plans to promote participant retention and complete follow-up {18b}

Each trial participant will receive a cell phone to enable the research team to contact them regarding their 6-month follow up.

#### Data management {19}

Each participant will be allocated a unique participant identification number which will be used on all electronic documents and photographs. Data will be collected by researchers in Nepal and entered on to the REDCap platform hosted on a secure server at the University of Birmingham. Ulcer photographs taken using the ARANZ® device will be saved to the secure SilhouetteCentral SQL server. Data will be encrypted and access will be password restricted.

#### Confidentiality {27}

All collected data will remain confidential. All data will be stored in accordance with GCP and General Data Protection Regulations 2018 (GDPR), and the Data Protection Act 2018.

#### Plans for collection, laboratory evaluation, and storage of biological specimens for genetic or molecular analysis {33}

None

### Analyses and inference

#### Statistical methods for main endpoints {20a}

##### Time to healing

Time to healing will be analysed using a Cox proportional hazards model with and without adjustment for baseline characteristics (trial ulcer area and participants’ age) allowing for right-censoring. For the rate of healing analysis, we will define the outcome as the ulcer size in cm^2^ at each time point and include in the model time since admission, treatment status and their interaction. Our parameter of interest will be that of the interaction term, which will be interpreted as the mean difference in rate of healing (in cm^2^ per unit time) between intervention and control groups. We will analyse this model using a linear mixed-effects model with participant-level random effects and both with and without adjustment for participant characteristics. Given there are multiple primary outcomes (two outcomes, with and without adjustment, for three types of ulcer assessment), we will adjust reported p values for multiple testing using a stepdown method, which provides an efficient means of controlling the family-wise error rate [25]. We will derive the approximate distributions of the test statistics to perform the stepdown procedure using a permutation test approach, by simulating 10,000 re-randomisations of the individuals [26].

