#### Sample size {14}

Sample size is based on the two primary outcomes: rate of healing and time to complete re-epithelialization. On the latter, we assume that 70% of ulcers will heal within 42 days with standard care [21]. Further, assuming that the intervention will increase this proportion to 90% and hazards are constant and proportional, for a two-sided test of the hazard ratio with a type I error of 5% and statistical power of 80% and a 1:1 allocation ratio, 47 individuals are required in each group. To allow for withdrawals and right censoring, we aim to recruit 65 patients in each group. We expect rate of healing to provide yet more precise estimates.

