##### Measurements

The above analyses of healing rate and time of complete re-epithelialisation will be made separately for each method of measurement. Photographs will be assessed blind to allocated treatment by two trained observers at the University of Birmingham (Fig. 2). Inter-rater reliability of the measurements will be made on 20% of ulcer photographs and assessed using interclass correlation coefficients.

Measurements are based on the ARANZ ® and tablet-based cameras (see Fig. 2). The ARANZ® images are measured in two ways: (1) manual tracings and (2) automatic tracings of wounds using a camera specifically designed to obtain standardised photographs of ulcers for scientific purposes. The distance of the camera from the ulcer surface is controlled by triangulation of three laser lights. The images taken by the camera in the tablet are calibrated digitally by reference to a measurement ruler in the frame. The areas (cm^2^) are then generated within the different software packages. We will measure, agreement between the methods of measurement:
The Push tool vs. the automated ARANZ® methodThe automated vs. manual ARANZ® method

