We are using three methods to measure the rate of ulcer healing and time to complete re-epithelialisation. Readers might wonder at such an extensive set of methods and consider this ‘overkill’. Our rationale for using these multiple ulcer measurement methods is two-fold. First, it is crucially important in our judgement to create a situation where results cannot be explained away by measurement error (for all that measurement error is more of a threat to precision than to accuracy). Second, we wish to contribute to the methodological literature on ulcer measurement. As investigators we hope that the results will be consistently null or positive (or even negative). However, we realise that we may end up with results that toggle around the conventional statistical threshold , say, according to ulcer measurement method or whether or not adjustment had been carried out for any discrepancy in ulcer size at base-line. In that case, we will simply report the different results and allow the reader to make an interpretation. We will not (miss) use statistical tests as decision rules.

By using a randomised control method, alongside standardised blindly assessed photographs, and information on activity, this research will provide robust evidence on the clinical and cost-effectiveness of L-PRF in the treatment of leprosy ulcers. Data collection and ulcer assessment follows a ‘closed-loop’ such that the photograph and image can follow only one pathway from camera to completed measurement. An additional benefit is the evaluation of the effects of treatment on quality of life for people living with the effects of leprosy. The findings will also be relevant to other ulcerative conditions, particularly diabetes, where ulcers similarly result from peripheral nerve damage. The results will improve our understanding of the scalability of this treatment across low-income countries for ulcer healing in leprosy and other similar conditions.

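### The article defines the primary family in two incompatible ways, and its 80% power is for a single unadjusted test rather than for the stepdown-adjusted analysis

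*Protocol article*

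**What the plan says.** - **Outcomes {12}** lists two main endpoints, rate of healing and time to complete re-epithelialization, each analysed with and without baseline adjustment. It then chooses between the two: "we prefer unadjusted outcomes in randomised studies and therefore declare them as" primary. It does not mention measurement method.
- **Time to healing, under {20a}**, describes the family as "Given there are multiple primary outcomes (two outcomes, with and without adjustment, for three types of ulcer assessment" and says "we will adjust reported p values for multiple testing using a stepdown method". The reference distribution is obtained "using a permutation test approach, by simulating 10,000 re-randomisations of the individuals".
- **Measurements**: "The above analyses of healing rate and time of complete re-epithelialisation will be made separately for each method of measurement".
- **Ulcer measurements** leaves the healing date to the local clinician, which gives one date per participant whatever the photographic method.
- **Sample size {14}** says it rests on both primary outcomes. The only calculation is "for a two-sided test of the hazard ratio with a type I error of 5% and statistical power of 80" per cent, giving 47 per group. Recruitment is raised to 65 per group for withdrawals and right censoring. No figure is given for rate of healing.
- **Discussion**, on results that differ by method or adjustment: "we will simply report the different results and allow the reader to make an interpretation".

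**The concern.** This is not detail deferred to an analysis plan. The article states the family twice, and the statements differ. From Outcomes {12} an analyst would build a family of two tests, or six if each method counts. From {20a} the analyst would build twelve. Using the clinician's date for time to healing collapses three method-specific versions into one, and the twelve become eight. A stepdown-adjusted p value depends on what else is in the family, so the reported primary p values are not fixed until this is settled.

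Most members of the larger family re-ask the same two questions. Unless they are identical tests, each addition raises the critical value for both. The interim rule speaks of two main endpoints, so it too needs one defined result per endpoint. The power statement describes a test with no multiplicity adjustment, which is not the test that {20a} plans.

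**Working it through.** **Inputs from Sample size {14}:** 70% of controls and 90% of intervention participants healed by 42 days; constant proportional hazards; two-sided 5%; 80% power; 1:1 allocation; 47 per group required; 65 per group recruited.

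**Reproducing the stated figure**
- Hazard ratio = ln(1 − 0.90)/ln(1 − 0.70) = ln(0.1)/ln(0.3) = 1.912; log hazard ratio 0.6484.
- Events (Schoenfeld) = 4 × (1.96 + 0.8416)² / 0.6484² = 74.7.
- Mean event probability = (0.70 + 0.90)/2 = 0.80, so total = 74.7/0.80 = 93.3, or 46.7 per group. This rounds to 47 and matches exactly. The full 5% is spent on one test.

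**Counting the family**
- {20a} as written: 2 outcomes × 2 adjustments × 3 methods = 12.
- With one clinician-dated healing time: 2 time-to-healing tests + (2 × 3) healing-rate tests = 8.
- Two endpoints, unadjusted, one lead method: 2.

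**Power under the stepdown**

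Power = Φ(0.6484 × √events / 2 − c), where c is the critical |z|.
- 47 evaluable per group: 94 × 0.80 = 75.2 events, signal 2.81.
- 65 analysed per group: 130 × 0.80 = 104 events, signal 3.31.

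The first-step c is the 95% point of the largest |z| in the family, simulated with 200,000 draws. The article gives no correlations. I assumed 0.7–0.95 within an outcome and 0.3–0.8 between outcomes. The later step assumes that all healing-rate tests have already been rejected.

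| Family | First-step c | 47 per group: first step, then later step | 65 per group: first step, then later step |
|---|---|---|---|
| 1 test | 1.96 | 80% | 91% |
| 2 tests | 2.15–2.24 | 72–75%, 80% | 86–88%, 91% |
| 8 tests | 2.33–2.61 | 58–68%, 73–77% | 76–84%, 87–89% |
| 12 tests | 2.40–2.73 | 53–66%, 63–73% | 72–82%, 80–86% |

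Worked example, 12 tests at 47 per group: Φ(2.81 − 2.73) ≈ 53% and Φ(2.81 − 2.40) ≈ 66%.

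**Bounds that need no correlation assumption.** Bonferroni over 12 tests (0.05/12 = 0.00417) gives a floor of 48% at 47 per group and 67% at 65. The ceiling for any given test is its unadjusted power, 80% and 91%.

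**Whole stepdown.** I also simulated the full 12-test procedure with correlations of 0.8–0.95 within and 0.5–0.8 between outcomes. The healing-rate signal ranged from nil to 1.2 times the time-to-healing signal. Power for a given time-to-healing test was about 58–75% at 47 per group and 77–88% at 65. Power to reject at least one hypothesis at 47 per group was about 75–95%.

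**The case against.** Four points can fairly be made for the plan.

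1. **The trial recruits 65 per group, not 47.** Missing data {20c} treats withdrawal before healing as a remote possibility, and dividing by 0.80 already accounts for ulcers unhealed at 42 days. A reader might infer that 53–66% is the power of this trial, or that the trial is underpowered. The article does not support that. With all 65 analysed, the 12-test power straddles 80% and the 8-test power exceeds it at the later step. This point stands.
2. **The procedure is efficient.** A permutation stepdown exploits correlation between tests, and identical tests cost nothing. The article expects rate of healing to be the more precise endpoint, which makes the later-step figures relevant. It also does not say whether power means a given test or at least one rejection. This stands, and it is why ranges are shown.
3. **The absence of a lead method is deliberate.** One might read it as an oversight, or as room for selective reporting. The Discussion explains why three methods are used, commits to reporting all results and declines to use tests as decision rules. That stance is legitimate. It does not remove the conflict with Outcomes {12}, which does choose a primary analysis, or with {20a}, which controls a family-wise error rate over a family that must be defined.
4. **Type I error is not inflated.** Adjusting over the larger family is conservative. This stands; the cost is in power and clarity.

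**Conclusion.** Two things are certain from the text. The article gives conflicting definitions of the primary family: {20a} against Outcomes {12}, and the single clinician-set healing date against the method-specific analyses in Measurements. The 80% is the power of one unadjusted test.

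At the 47 evaluable per group for which 80% is stated, the adjusted power for a given time-to-healing test cannot exceed the unadjusted 80%. It is lower at the first step for every family larger than one. The size of the loss, to about 53–66% (12 tests) or 58–68% (8 tests) at the first step, rests on assumed correlations. For the recruited 130, a shortfall is possible but not shown. The count of twelve is itself unsettled and should not be quoted as fixed. This is a should-fix point about definition and stated power; it does not show that the design fails.

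**What to change.** 1. Make Outcomes {12}, Ulcer measurements, Time to healing under {20a}, and Measurements agree on one primary family. Say whether time to healing uses the clinician's date or varies by photographic method.
2. Preferably, limit the family to the unadjusted analysis of each of the two endpoints. Use one lead measurement method wherever an endpoint depends on method, chosen by the sponsor before unblinding. The article gives no basis for a reviewer to pick it.
3. Report every other combination of method and adjustment in full, as sensitivity analyses outside the family. This keeps the Discussion's aim of showing all results.
4. In Sample size {14}, say that 80% is the unadjusted power, and give the family-adjusted power for 47 evaluable and 65 recruited per group. For two tests this is about 72–75% and 86–88% at the first step, and 80% and 91% at the second.

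The cost is wording only, with no new data or participants. The stated power at 47 per group looks slightly less favourable. In return, under the same assumptions, first-step power at 47 per group rises from 53–66% with twelve tests to 72–75% with two.
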